**Participant Population(s) Checklist****Yes/No**

- Children (under 18) N
- Pregnant Women and Fetuses N
- Neonates (0 - 28 days) N
- Abortuses N
- Prisoners N
- International Participants N
- Please enter the countries separated by comma
- Impaired Decision Making Capacity N
- Cancer Subjects N
- Laboratory Personnel N
- Healthy Volunteers N
- Students N
- Stanford students N Other students N
- Employees N
- Other (i.e., any population that is not specified above) Y

**Study Location(s) Checklist****Yes/No**

- Stanford University Y
- Clinical & Translational Research Unit (CTRU)
- Stanford Medicine Health Care Y
- Tri-Valley
- Stanford Medicine Children's Health
- VAPAHCS (Specify PI at VA)
- Other (Click ADD to specify details)

**Title :** Immune system modulation by enhanced vs standard prehabilitation program in patients undergoing elective major surgery - a prospective monocentric randomized single-blinded control . . .

**Approval Period:** 10/23/2023 - 12/31/2999

**General Checklist****Multi-site****Yes/No**

- Is this a multi-site study? A multi-site study uses the same protocol to conduct human subjects research at more than one site.

N

**Cooperative/Collaborative Study?****Yes/No**

- Are there any collaborating institution(s)? A collaborating institution is generally an institution that collaborates equally on a research endeavor with one or more institutions.

N

**Cancer Institute****Yes/No**

- Cancer-Related Studies (studies with cancer endpoints), Cancer Subjects (e.g., clinical trials, behavior/prevention) or Cancer Specimens (e.g., blood, tissue, cells, body fluids with a scientific hypothesis stated in the protocol).

N

**Clinical Trials****Yes/No**

- Investigational drugs, biologics, reagents, or chemicals? N
- Commercially available drugs, reagents, or other chemicals administered to subjects that are being studied? N
- Investigational Medical Device / Commercial Medical Device used off-label or if being studied? N
- IDE Exempt Device (Commercial Medical Device used according to label, Investigational In Vitro Device or Assay, or Consumer Preference/Modifications/Combinations of Approved Medical Devices) N
- Will this study be registered on clinicaltrials.gov? ( See Stanford decision tree ) Y
- Who will register for ClinicalTrials.gov?  
NCT# 04498208 Y

**Tissues and Specimens****Yes/No**

- Human blood, cells, tissues, or body fluids (tissues)? Y
- Tissues to be stored for future research projects? N
- Tissues to be sent out of this institution as part of a research agreement? For guidelines, please see Material Transfer Agreements N

**Biosafety (APB)****Yes/No**

- Are you submitting a Human Gene Transfer investigation using a biological agent or

N

**Title :** Immune system modulation by enhanced vs standard prehabilitation program in patients undergoing elective major surgery - a prospective monocentric randomized single-blinded control . . .

**Approval Period:** 10/23/2023 - 12/31/2999

recombinant DNA vector? If yes, please complete the Gene Transfer Protocol Application Supplemental Questions and upload in Attachments section.

- Are you submitting a Human study using biohazardous/infectious agents? If yes, refer to the <https://ehs.stanford.edu/forms-tools/genome-editing-and-gene-drives-stanford> Administrative Panel on BioSafety website prior to performing studies. N
- Are you submitting a Human study using samples from subjects that are known or likely to contain biohazardous/infectious agents? If yes, refer to the <https://ehs.stanford.edu/forms-tools/genome-editing-and-gene-drives-stanford> Administrative Panel on BioSafety website prior to performing studies. N

### Human Embryos or Stem Cells

**Yes/No**

- Human Embryos or Gametes? N
- Human Stem Cells (including hESC, iPSC, cancer stem cells, progenitor cells) N

### Veterans Affairs (VA)

**Yes/No**

- The research recruits participants at the Veterans Affairs Palo Alto Health Care System(VAPAHCS). N
- The research involves the use of VAPAHCS non-public information to identify or contact human research participants or prospective subjects or to use such data for research purposes. N
- The research is sponsored (i.e., funded) by VAPAHCS. N
- The research is conducted by or under the direction of any employee or agent of VAPAHCS (full-time, part-time, intermittent, consultant, without compensation (WOC), on-station fee-basis, on-station contract, or on-station sharing agreement basis) in connection with her/his VAPAHCS responsibilities. N
- The research is conducted using any property or facility of VAPAHCS. N

### Equipment

**Yes/No**

- Use of Patient related equipment? If Yes, equipment must meet the standards established by Biomedical Engineering (BME) [contact]) N
- Medical equipment used for human patients/subjects also used on animals? N
- Radioisotopes/radiation-producing machines, even if standard of care? ; More Info N

### Payment

**Yes/No**

- Subjects will be paid/reimbursed for participation? See payment considerations. N

### Funding

**Yes/No**

- Training Grant? N

**Title :** Immune system modulation by enhanced vs standard prehabilitation program in patients undergoing elective major surgery - a prospective monocentric randomized single-blinded control . . .

**Approval Period:** 10/23/2023 - 12/31/2999

- |                                      |   |
|--------------------------------------|---|
| • Program Project Grant?             | N |
| • Federally Sponsored Project?       | N |
| • Industry Sponsored Clinical Trial? | N |

**Funding****Funding - Grants/Contracts/Agreements****Funding - Fellowships****Gift Funding****Dept. Funding**

**Department Name :** Anesthesiology and  
Perioperative Medicine

**Other Funding**

**Other Fund Name :** [name] faculty start-up  
funds

**Resources :****a) Qualified staff.****Please state and justify the number and qualifications of your study staff.**

- > [name], colorectal surgeon at Stanford, PD of study - responsible for protocol development
- > [name] PhD, PI of study,  
- responsible for enrolling subjects, data collection, data analysis, interpretation, and overseeing all aspects of the study
- > [name], [name], [name] - data collection, data analysis, interpretation, protocol development, coaching
- > [name] - data management, OnCore updates

**b) Training.****Describe the training you will provide to ensure that all persons assisting with the research are informed about the protocol and their research-related duties and functions.**

The entire team will have an in-person or phone/teleconference meeting weekly to discuss the protocol, enrollment issues, data collection issues, and data analysis and interpretation.

**c) Facilities.**

**Title :** Immune system modulation by enhanced vs standard prehabilitation program in patients undergoing elective major surgery - a prospective monocentric randomized single-blinded control . . .

**Approval Period:** 10/23/2023 - 12/31/2999

**Provide the location(s) where the research will be conducted, including physical address if not conducted on site at Stanford University, Stanford Hospital on [name], Lucile Packard Children's Hospital on [name] or VAPAHCS. Describe the facilities and resources available to conduct the research at these sites.**

Stanford Health Care: surgical patients will undergo study enrollment and education in the outpatient general surgery clinics  
Stanford Department of Surgery: This is where the data analysis and interpretation will occur.

**d) Sufficient time.**

**Explain the time that you and your research team will allocate to perform the research activities, including data analysis.**

Our goal enrollment is 120 patients. We anticipate that we will enroll 6 patients a month, so we estimate that we will enroll patients for 13 months and follow them for 3 months (Total 16 months).

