- > Adherence to prehab programs using a modified "Rehabilitation Adherence Measure for Athletic Training" scale
- > Physical status assessment including 6 Minute Walk Test (6MWT), Timed Up and Go (TUG), Five Times Sit to Stand Test & Wall Squat Test and Body Mass Index (BMI)
- > Prevalence and global severity of anxiety using questionnaires such as the APAIS (Amsterdam Preoperative Anxiety and Information Scale) and the Pain catastrophization scale.
- > Cognitive status evaluated by the qMCI

We will also evaluate the effect of prehab programs on post-operative outcomes by collecting:

- > Hospital length of stay
- > Readmission within 30 days after surgery
- > Postoperative complications scored by the Comprehensive Complication Index (CCI) within 90 days after surgery
- > Inpatient opioid use and pain levels during hospitalization
- > Neuropathic pain, quality of life and cognitive function assessed 30 days after surgery (in comparison to before surgery)

If the intervention is found to be clearly harmful then the study will be terminated before the total projected participant population has been enrolled. This will be determined by assessing for increase in complication rates after surgery beyond our baseline rates of complications (as determined by NSQIP data). These rates will be

**Title :** Immune system modulation by enhanced vs standard prehabilitation program in patients undergoing elective major surgery - a prospective monocentric randomized single-blinded control . . .

**Approval Period:** 10/23/2023 - 12/31/2999

calculated on a quarterly basis.

The study will end after complete enrollment (120 patients) or after 16 months of enrollment into the prehab intervention if no important differences are detected.

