## 8. Participant Population

- a) **State the following: (i) the number of participants expected to be enrolled at Stanford-affiliated site(s); (ii) the total number of participants expected to enroll at all sites; (iii) the type of participants (i.e. students, patients with certain cancer, patients with certain cardiac condition) and the reasons for using such participants.**

(i) 120 patient participants total from Stanford Health Care. 15 surgeons from SHC.  
(ii) total = 120 participants (only one site included in this study). 15 surgeons from SHC  
(iii) participants will be patients undergoing elective major surgery. Reasons for using this group of patients is that they have a baseline significant risk of post-operative complications including surgical site infections

**Title :** Immune system modulation by enhanced vs standard prehabilitation program in patients undergoing elective major surgery - a prospective monocentric randomized single-blinded control . . .

**Approval Period:** 10/23/2023 - 12/31/2999

and readmissions. Finally, patients undergoing major abdominal surgery often feel overwhelmed, or a sense of loss of control over their bodies; therefore, we hope that this intervention would help support them and also give them a sense of agency in their own recovery and health.

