**l) Costs. Please explain any costs that will be charged to the participant.**

There will be no costs that will be charged to the participants.

**m) Estimate the probable duration of the entire study. Also estimate the total time per participant for: (i) screening of participant; (ii) active participation in study; (iii) analysis of participant data.**

Probable duration of the entire study: 6 months

Per participant:

(i) screening: 15 minutes

(ii) active participation in study: 90 days

(iii) analysis of data: 1 hour

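### At the stated 6 patients a month, 13 months of enrolment gives 78 patients, not the target of 120, and the study-end rule and the stated study duration do not fit that timetable either

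*Protocol*

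**What the plan says.** The target is the same wherever it appears. Resources d) says "Our goal enrollment is 120 patients", and section 8a says "120 patient participants total from Stanford Health Care" and describes a single site.

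The timetable is given in three places:

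- Resources d), Sufficient time: "We anticipate that we will enroll 6 patients a month, so we estimate that we will enroll patients for 13 months", then "follow them for 3 months (Total 16 months".
- Section 2g, Study Endpoint: "The study will end after complete enrollment (120 patients) or after 16 months of enrollment into the prehab intervention if no important differences are detected".
- Section 8m: "Probable duration of the entire study: 6 months". On separate lines below it are the times per participant, including "active participation in study: 90 days".

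Section 9d also bears on the end of the study. It says that stopping before everyone has been enrolled is not planned.

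**The concern.** Resources d) presents the enrolment period as a consequence of the monthly rate, yet the two do not multiply to the target. The number 16 then changes meaning: in Resources d) it is the length of the whole study, and in 2g it is a limit on enrolment. Section 8m gives a third, much shorter duration.

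The 2g wording makes this more than a feasibility estimate. It makes calendar time one of the conditions that can end the study. If the calendar and the rate do not deliver 120, the protocol does not settle how many patients a trial that shows no difference would have when it closes. Fewer patients mean wider intervals, which matters most when the result is to be read as showing no difference.

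**Working it through.** **Inputs**

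- Target N = 120 (Resources d, 2g, 8a).
- Rate r = 6 patients a month (Resources d).
- Enrolment period 13 months, follow-up 3 months, total 16 months (Resources d).
- Enrolment limit 16 months, conditional (2g).
- Entire study 6 months (8m).
- Enrolment at least 28 days before surgery (section 2a); complications counted to 90 days after surgery (2g).

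**Step 1. Reproduce the plan's figure.** Expected enrolment = rate x months.

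- 6 x 13 = 78. This is 120 - 78 = 42 short (35%); 78/120 = 65%.

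The target is not reproduced.

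**Step 2. Try other readings.**

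- 6 per arm per month, two arms: 6 x 2 x 13 = 156. Too many.
- 16 months of enrolment, as in 2g: 6 x 16 = 96. This is 24 short (20%); 96/120 = 80%.
- Enrolment throughout the 6 months of 8m: 6 x 6 = 36 (30%). With 3 of those months kept for follow-up: 6 x 3 = 18.
- 78 inflated for dropout: 78/(1 - d) = 120 only if d = 35%. The protocol states no such rate, and 120 is itself described as enrolment, so dropout cannot close the gap.

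**Step 3. What would be consistent.**

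- Keep the rate: 120/6 = 20 months of enrolment; 20 + 3 = 23 months in total.
- Keep 13 months: 120/13 = 9.2 patients a month.
- Keep 16 months as enrolment: 120/16 = 7.5 patients a month.
- Keep 6 months for everything: 120/6 = 20 a month with no follow-up time, or 120/3 = 40 a month with 3 months of follow-up.

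The 23 months takes the stated 3-month follow-up as it stands. Counted from enrolment, the last patient needs at least 28 + 90 = 118 days, about 3.9 months, so the total would be about 24 months or more.

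**Step 4. Compare the durations.**

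- Within Resources d): 13 + 3 = 16. Consistent.
- Resources d) against 2g: 16 months is the total in one and an enrolment limit in the other.
- 8m against both: 6 months is shorter than the 13-month enrolment period alone.

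**Step 5. Effect on precision.** With the same split between arms, standard errors scale with 1/sqrt(N).

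- 96 patients: sqrt(120/96) = 1.12.
- 78 patients: sqrt(120/78) = 1.24.

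For illustration only, assume a two-sample comparison of means, 1:1 allocation, two-sided 5% alpha, 80% power and no dropout. The detectable standardised difference is (1.960 + 0.842) x 2/sqrt(N): 0.51 SD at 120, 0.57 SD at 96 and 0.63 SD at 78. The protocol states none of these assumptions. Other choices of alpha and power move all three values but leave their ratios at 1.12 and 1.24.

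**The case against.** The strongest reply is that Resources d) and 8m are feasibility answers on an ethics-board form, worded as expectations. They do not touch randomisation, endpoints or analysis. The target of 120 never varies, and actual accrual may be faster than 6 a month. That is fair as to weight, but no higher rate is stated, and the 13 months is given as the result of the 6.

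Three stronger readings are tempting, and the document does not support them.

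- A reader might infer that 13, 16 and 6 months all contradict one another. They do not: 13 and 16 agree inside Resources d). The conflicts come from 2g, which uses 16 for enrolment, and from 8m. If 2g is read as an upper limit and not a plan, its tension with 13 months softens. The shortfall at 16 months and the conflict with 6 months remain.
- A reader might infer that the trial will stop at 96 patients. The 2g limit applies only if no important differences are detected, and 9d points the other way. Stopping at about 96 is one reading of passages that disagree.
- A reader might infer that the months are wrong and the rate is right. The document does not say which input is the error.

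**Conclusion.** The timetable is wrong as written. At the protocol's own rate, 13 months yields 78 patients, 65% of the target, and no ordinary reading recovers 120. The conditional 16-month enrolment limit in 2g would be met at about 96 patients (80%), before the target, and it conflicts with 9d. The 6 months in 8m cannot hold with either figure.

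These results rest only on the stated rate, months and target. The loss of precision, standard errors about 1.12 times (96) or 1.24 times (78) those at 120, assumes only that the arms shrink in proportion. The detectable differences in SD units are illustrative and should not be read as the trial's planned power.

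What is established is that the rate, the calendar and the target do not fit together, and that the study-end rule depends on them. It is not established that the trial will close short.

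**What to change.** Reconcile the rate, the enrolment period and the target, and put the same figures in Resources d), 2g and 8m. The sponsor has to say which input was wrong:

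- If 6 a month stands, state 20 months of enrolment and at least 23 months in total with the 3-month follow-up. State a longer total if the 28 or more days before surgery and the 90-day post-operative window are counted from enrolment.
- If 13 months stands, state the rate of about 9.2 a month that 120 requires, and why it is attainable.
- Otherwise restate the planned size, with its adequacy considered and not taken from the calendar alone.

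In 2g, set the calendar limit so that it does not fall before 120 patients at the stated rate, say whether it counts enrolment or total time, and reconcile it with 9d. In 8m, replace the 6 months with the agreed total.

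The cost is a wording amendment in these places. Unless the planned size is restated, it stays at 120 patients. The downside is a less favourable stated timeline if the rate of 6 a month is kept.

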**e) Access to target population.**

**Explain and justify whether you will have access to a population that will allow recruitment of the required number of participants.**

As the PD is a surgeon who works closely with other surgeons in multiple departments, we have direct access to the surgery patient population. Our research workflow is well-embedded into the clinical workflow as we have been enrolling patients in these clinics since 2018.

**f) Access to resources if needed as a consequence of the research.**

**State whether you have medical or psychological resources available that participants might require as a consequence of the research when applicable. Please describe these resources.**

We do not anticipate any medical or psychological consequences as a result of the study. However, as the PI is a practicing surgeon, we have access to medical or psychological resources that participants might require.

**g) Lead Investigator or Coordinating Institution in Multi-site Study.**

**Please explain (i) your role in coordinating the studies, (ii) procedures for routine communication with other sites, (iii) documentation of routine communications with other sites, (iv) planned management of communication of adverse outcomes, unexpected problems involving risk to participants or others, protocol modifications or interim findings.**

## Expedited Form

**A protocol must be no more than minimal risk (i.e., "not greater than those ordinarily encountered in daily life") AND must only involve human subjects in one or more of the following paragraphs.**

**Select one or more of the following paragraphs:**

**1. N Clinical studies of drugs and medical devices only when condition (a) or (b) is met.**

- a) Research on drugs for which an investigational new drug application (21 CFR Part 312) is not required. (Note: Research on marketed drugs that significantly increases the risks or decreases the acceptability of the risks associated with the use of the product is not eligible for expedited review.)
- b) Research on medical devices for which
  - i) an investigational device exemption application (21 CFR Part 812) is not required; or

**Title :** Immune system modulation by enhanced vs standard prehabilitation program in patients undergoing elective major surgery - a prospective monocentric randomized single-blinded control . . .

**Approval Period:** 10/23/2023 - 12/31/2999

- ii) the medical device is cleared/approved for marketing and the medical device is being used in accordance with its cleared/approved labeling.

**2. N Collection of blood samples by finger stick, heel stick, ear stick, or venipuncture as follows:**

- a) from healthy, nonpregnant adults who weigh at least 110 pounds. For these subjects, the amounts drawn may not exceed 550 ml in an 8 week period and collection may not occur more frequently than 2 times per week; or
- b) from other adults and children, considering the age, weight, and health of the subjects, the collection procedure, the amount of blood to be collected, and the frequency with which it will be collected. For these subjects, the amount drawn may not exceed the lesser of 50 ml or 3 ml per kg in an 8 week period and collection may not occur more frequently than 2 times per week.

**3. N Prospective collection of biological specimens for research purposes by non invasive means.**

**4. Y Collection of data through non invasive procedures (not involving general anesthesia or sedation) routinely employed in clinical practice, excluding procedures involving x-rays or microwaves. Where medical devices are employed, they must be cleared/approved for marketing. (Studies intended to evaluate the safety and effectiveness of the medical device are not generally eligible for expedited review, including studies of cleared medical devices for new indications.)**

**Examples:**

- a) physical sensors that are applied either to the surface of the body or at a distance and do not involve input of significant amounts of energy into the subject or an invasion of the subject's privacy;
- b) weighing or testing sensory acuity;
- c) magnetic resonance imaging;
- d) electrocardiography, electroencephalography, thermography, detection of naturally occurring radioactivity, electroretinography, ultrasound, diagnostic infrared imaging, doppler blood flow, and echocardiography;
- e) moderate exercise, muscular strength testing, body composition assessment, and flexibility testing where appropriate given the age, weight, and health of the individual.

**5. N Research involving materials (data, documents, records, or specimens) that have been collected, or will be collected solely for nonresearch purposes (such as medical treatment or diagnosis). (NOTE: Some research in this paragraph may be exempt from the HHS regulations for the protection of human subjects. 45 CFR 46.101(b)(4). This listing refers only to research that is not exempt.)**

